#### Secondary endpoints

2.6.2

Secondary endpoints involve the occurrence of MACEs, defined as all-cause mortality, cardiac death, a first or recurrent, non-fatal, acute myocardial infarction, target lesion revascularization (PCI or CABG), stroke, heart failure and cardiac rehospitalization within 1, 6, and 12 months post-PCI. Other secondary endpoint will include changes in myocardial viability in the territory supplied by the CTO artery between the baseline and 12 months post-PCI, to be determined by CMR. In addition, QOL changes at 1, 6, and 12-month follow-up appointments will be assessed by comparing with baseline values using the SAQ, patient health questionnaire 9 and Generalized Anxiety Disorder Scale -7. Finally, the volume of contrast used during the procedure and the total cost of medical care covering OMT and the equipment for coronary artery disease therapy from the day of enrollment (first hospitalization) to the last follow-up (rehospitalization) will be evaluated. Perioperative myocardial infarction will be evaluated by assessing CK, CK-MB, and cTNI levels;

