### Study design and randomization

2.1

This SOS-moral study is a randomized controlled trial with a multi-center design. The protocol was approved by the ethics committee of Beijing Anzhen Hospital (approval no. 2017059X) and has been registered at ClinicalTrials.gov (identifier: NCT 03372785).

Patients meeting the inclusion criteria will be categorized into two groups at a ratio of 1:1 according to a randomized digital table used to randomly assign patients to the CTO-PCI group (PCI of both the non-CTO artery and a concurrent CTO artery), or the non-CTO PCI group (PCI of only the non-CTO artery). The randomized digital form and interactive voice response mode will be applied to facilitate the randomization procedure. The randomization sequence will be produced and managed by an independent staff member. Before intervention, myocardial viability and cardiac function of patients will be evaluated using CMR. Cardiac function will be assessed using transthoracic echocardiography and CMR. The Seattle angina questionnaire (SAQ), Patient Health Questionnaire 9 and Generalized Anxiety Disorder Scale-7 will be used to evaluate patient QOL. Cardiac function, QQL, and MACE will be observed within 12 months of follow-up. A flow chart outlining the study design is depicted in Figure 1.

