### Treatment groups

2.2

Patients in the CTO-PCI group receive PCI treatment involving both the CTO artery and the non-CTO artery. Patients of the non-CTO PCI group will only have PCI performed on the non-CTO artery. To ensure safety of all patients, they will be monitored, and those with persisting clinical symptoms occurring within one month of OMT will undergo PCI of CTO artery.

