### Sample size calculation

2.7

PASS 15.0 will be utilized to calculate sample size. In the study, 226 individuals are predicted to be recruited in the trial. This sample size was calculated using the optimal efficiency test. The main purpose of this trial is to investigate the effect successfully opening concurrent CTO lesions on cardiac function in patients with MVD. LVEF has been taken into consideration for the calculation of sample size. Previous studies revealed a 6.5% mean difference between the two experimental groups and a 9% standard deviation with respect to LVEF. The optimal boundary value for LVEF was set to 4%.^[21]^ Two-hundred sixteen cases recruited to the study will allow for the use of a 1-tailed test with a significance level (α) set to 0.025, and power (1-β) of 0.90. Ultimately, it is estimated that 240 patients will be randomized, and a 10% loss is expected to occur throughout the 1-year follow-up period.

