### Statistical analysis

2.8

In the full analysis set, all randomized patients will be kept in the treatment group to which they were originally randomized. Moreover, patients without protocol deviation will be included in the per protocol set. Patients of the per protocol set will be included in baseline information analysis rather than in primary analysis if the CTO-PCI fails. Patients will not be included in the primary analysis if the MACEs occur.

Continuous variables normally distributed will be presented as means ± standard deviation, and student *t*-test will be used to make comparisons between two independent samples. Median and 4-quintile intervals will be used to express variables that are not normally distributed, and the Mann–Whitney *U*-test will be used to compare differences. Categorical variables will be presented as frequencies and percentages, and the differences between groups will be assessed using a chi-square test. Survival analysis will be performed using a Kaplan–Meier curve and Cox regression analysis. A 2-sided *P*-value < .05 will be considered statistically significant.

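### The MACE component of target lesion revascularization is tied to treated lesions in a trial whose arms treat different lesions, and its direction can turn on an undefined term

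*Protocol article*

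**What the plan says.** In the protocol article, section 2.6.2 (Secondary endpoints) builds MACE from death, infarction and further components, among them "target lesion revascularization (PCI or CABG), stroke, heart failure and cardiac rehospitalization within 1, 6, and 12 months post-PCI". It does not say which lesions are target lesions.

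Section 2.2 (Treatment groups) fixes what is treated. For one arm: "Patients in the CTO-PCI group receive PCI treatment involving both the CTO artery and the non-CTO artery". For the other: "Patients of the non-CTO PCI group will only have PCI performed on the non-CTO artery". The same section says that, among monitored patients, "those with persisting clinical symptoms occurring within one month of OMT will undergo PCI of CTO artery". No stated rule says whether that procedure counts as a MACE.

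Section 2.8 (Statistical analysis) gives the method for time-to-event outcomes: "Survival analysis will be performed using a Kaplan–Meier curve and Cox regression analysis". It also ties MACE to the main LVEF comparison: "Patients will not be included in the primary analysis if the MACEs occur".

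**The concern.** A lesion-specific endpoint compares like with like when both arms have the same lesions treated. Here the arms differ by design in exactly that respect. The revascularization component then depends on how many lesions were treated and on the rule in section 2.2 for later CTO-PCI, as well as on how well the treated lesions hold up.

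Two natural readings give the arms different exposure:

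- **Reading A: a target lesion is one treated at index.** The CTO-PCI arm carries an additional lesion that can generate an event. Later CTO-PCI in a control patient is not a target lesion event.
- **Reading B: the CTO is a target lesion in both arms.** Later CTO-PCI under section 2.2 becomes an event, and it falls mainly on controls.

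At stake is the size, and possibly the direction, of one component of a secondary composite. There is also a possible effect on the primary analysis, through the exclusion of patients with MACE in section 2.8.

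**Working it through.** The article states no MACE or revascularization rate, so there is no figure of its own to reproduce. What follows is an illustration of how far the definition alone can move the component.

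**Inputs from the article**
- Allocation is "categorized into two groups at a ratio of 1:1" (section 2.1), and "it is estimated that 240 patients will be randomized, and a 10% loss is expected to occur" (section 2.7). That gives 240 / 2 = 120 per arm.
- CTO-PCI success is intended to be above 80% (section 2.4.1). I use s = 0.80.

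**Assumptions, not in the article**
- One non-CTO lesion is treated per patient. Section 2.3.1 requires at least one other diseased major vessel, so there may be more.
- The 12-month repeat revascularization risk per successfully treated lesion is r = 3%, 5% or 8%, the same for both lesion types and both arms, and independent between lesions.
- The share of controls who have later CTO-PCI under section 2.2 is c = 5%, 10% or 20%, that is 6, 12 or 24 of 120.
- Repeat attempts after a failed CTO-PCI are ignored.

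**Reading A**
- CTO-PCI arm: 1 − (1 − r)(1 − 0.8r)
- Control arm: r

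At r = 5%: 1 − 0.95 × 0.96 = 0.088, against 0.050. Per 120 patients this is 10.56 v 6.0, an excess of about 4.6.

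| r | CTO-PCI | Control | Difference (points) |
|---|---|---|---|
| 3% | 5.3% | 3.0% | +2.3 |
| 5% | 8.8% | 5.0% | +3.8 |
| 8% | 13.9% | 8.0% | +5.9 |

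The differences arise although every treated lesion performs identically.

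**Reading B**
- CTO-PCI arm: as above
- Control arm: 1 − (1 − r)(1 − c)

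At r = 5% and c = 10%: 1 − 0.95 × 0.90 = 0.145, against 0.088.

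| r | CTO-PCI | Control, c = 5% | Control, c = 10% | Control, c = 20% | Differences (points) |
|---|---|---|---|---|---|
| 3% | 5.3% | 7.9% | 12.7% | 22.4% | −2.5, −7.4, −17.1 |
| 5% | 8.8% | 9.75% | 14.5% | 24.0% | −0.95, −5.7, −15.2 |
| 8% | 13.9% | 12.6% | 17.2% | 26.4% | +1.3, −3.3, −12.5 |

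**Where the sign changes.** Under Reading B the arms are equal when (1 − r)(1 − 0.8r) = (1 − r)(1 − c), that is when c = 0.8r. So c above 2.4%, 4.0% or 6.4% (for r = 3%, 5%, 8%) turns the contrast against controls. Under Reading A it always goes against the CTO-PCI arm.

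**A third reading** counts only the non-CTO lesions treated at index. Both arms then have risk r and the difference is zero. It is symmetric, but it misses re-intervention on the CTO, and the article does not say that it is meant.

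**The case against.** The strongest reply has four parts.

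1. **The term is merely undefined here.** A condensed article can leave a counting rule to the full protocol or the analysis plan, neither of which is shown, and section 2.9 has senior experts helping to identify MACEs. This stands as far as the absence of a rule goes. It does not cover the choice of a lesion-specific component, which is stated, next to treatment arms that differ in lesions treated, which is also stated.

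2. **These are effects of strategy, not bias.** Re-intervention on an additional treated lesion is a real consequence of opening the CTO, and later CTO-PCI is a real consequence of leaving it closed. This stands in part. A strategy comparison should count both. Reading A counts only the first, and Reading B mixes in treatment that the protocol itself directs.

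3. **The composite is less affected than the component.** Cardiac rehospitalization is also in MACE without qualification, so an admission for repeat revascularization or later CTO-PCI may enter by that route whatever the target lesion label. This stands. The figures above are for the component only.

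4. **The rates are assumed, and MACE is secondary.** This also stands. The article concedes in its conclusions that it may lack power for MACE. That concession concerns precision, however, and unequal exposure would not shrink with more patients.

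A reader might go further and infer that the component is asymmetric on any reading, that later CTO-PCI is an event only controls can have, or that the protocol counts it inconsistently. The article does not support these. The non-CTO-only reading is symmetric. Section 2.2 does not restrict later CTO-PCI to controls, and a failed CTO-PCI could be followed by another attempt. No counting rule is stated, so none can be called inconsistent.

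**Conclusion.** The point holds as a flaw in one component of a secondary composite, and it should be corrected. Under the usual meaning of target lesion, the CTO-PCI arm has one more lesion at risk: 8.8% v 5.0%, or about 4.6 patients per 120, at an assumed 5% per-lesion risk and 80% CTO-PCI success, with a range of +2.3 to +5.9 points over 3–8% risk. If the CTO is a target in both arms, the difference runs from +1.3 to −17.1 points over the assumed 5–20% of controls with later CTO-PCI. The direction of the component can therefore depend on an undefined term. These sizes rest on assumed rates and on one non-CTO lesion per patient. The effect on the whole composite is smaller and cannot be fixed from the article.

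A reader might also infer that the reading of target lesion decides who is dropped from the LVEF comparison. The article supports only that it may affect this. Patients with MACE are excluded there, but some of the same patients could be excluded through cardiac rehospitalization regardless. That exclusion is a separate and larger problem.

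**What to change.** 1. Define the revascularization component by the same vessels in both arms, for example any clinically driven coronary revascularization (PCI or CABG).
2. State whether PCI of the CTO artery under section 2.2 counts as an event, and whether the admission for it counts as cardiac rehospitalization. Apply one rule to both arms and report these procedures as their own category. Avoid relying on the word unplanned, since PCI that the protocol directs in advance could be placed on either side of it.
3. Report revascularization of the non-CTO lesions treated at index separately. These are at risk in both arms and give the like-for-like comparison.

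The cost is endpoint wording and one extra tabulation. The downside is that an any-revascularization component partly reflects the section 2.2 rule for later CTO-PCI, which is why items 2 and 3 should accompany it. Nothing here changes who receives CTO-PCI.

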#### Safety endpoints

2.6.3

The safety of the perioperative period, including acute coronary artery occlusion, acute vascular perforation, acute stent thrombosis, acute myocardial infarction, and cardiac death of the two groups assessed, will be compared.

### Sample size calculation

2.7

PASS 15.0 will be utilized to calculate sample size. In the study, 226 individuals are predicted to be recruited in the trial. This sample size was calculated using the optimal efficiency test. The main purpose of this trial is to investigate the effect successfully opening concurrent CTO lesions on cardiac function in patients with MVD. LVEF has been taken into consideration for the calculation of sample size. Previous studies revealed a 6.5% mean difference between the two experimental groups and a 9% standard deviation with respect to LVEF. The optimal boundary value for LVEF was set to 4%.^[21]^ Two-hundred sixteen cases recruited to the study will allow for the use of a 1-tailed test with a significance level (α) set to 0.025, and power (1-β) of 0.90. Ultimately, it is estimated that 240 patients will be randomized, and a 10% loss is expected to occur throughout the 1-year follow-up period.

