Early studies reported that successful recanalization CTO can both improve LVEF and ventricular wall movement assessed by CMR, and can improve QOL.^[22–25]^ An early meta-analysis found that successful recanalization of a CTO resulted in an overall improvement of 4.44% absolute LVEF points, reduced remodeling, and improved survival (OR: 0.52).^[26]^ However, the EXPLORE trial showed that in acute STEMI patients with concurrent CTO, CTO-PCI did not increase global LVEF or decrease LVEDV assessed by CMR 4-month post-PCI compared to patients receiving treatment in the non-CTO artery. Interestingly, a subgroup analysis of the EXPLORE trial showed that CTO-PCI in patients with a concurrent CTO in the LAD was associated with significantly higher LVEF levels after 4-month post-PCI compared with non-CTO PCI, suggesting that CTO-PCI may potentially benefit high-risk patients.^[19]^ According to Chung,^[27]^ the benefit of CTO-PCI is controversial with respect to cardiac function and survival among the MVD patients with concurrent CTO. This may partly be because myocardial viability affects the alteration of cardiac function produced by CTO-PCI. An in-depth analysis in the EXPLORE CMR study revealed that CTO-PCI was associated with the greater recovery of regional systolic function relative to baseline values 4-month post PCI in dysfunctional myocardial tissue supplied via CTO. The benefit was most evident in dysfunctional but viable segments (transmural extent of infarction <50%).^[28]^ The investigators opined that the benefit was probably attributable to the recovery of stunned myocardial tissue affected by the acute interruption of blood supply, as well as by the prevention of arrhythmia. Taken together, the data suggest that varying levels of myocardial viability in patients included in previous studies may be associated with reported variations in cardiac functioning observed after successful CTO-PCI treatments. Therefore, myocardial viability should be considered.

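### Section 2.7's inputs do not fit together: 216 patients follows only from a 4-point difference tested against zero, the 6.5-point difference then goes unused, and 226 matches nothing

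*Protocol article*

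**What the plan says.** All the design figures stand in section 2.7 (Sample size calculation) of the protocol article.

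- Effect and spread: "Previous studies revealed a 6.5% mean difference between the two experimental groups and a 9% standard deviation with respect to LVEF".
- A second effect-like figure, in percent: "The optimal boundary value for LVEF was set to 4". It cites a reference and is not defined further.
- The method: "This sample size was calculated using the optimal efficiency test". This term is not explained.
- Error rates: a "1-tailed test with a significance level (α) set to 0.025, and power (1-β) of 0.90".
- The size tied to those error rates: "Two-hundred sixteen cases recruited to the study will allow for the use of a 1-tailed test".
- The randomised number: 240, allowing for 10% loss over one year.
- A further number, earlier in the same paragraph: "226 individuals are predicted to be recruited in the trial".

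Section 2.1 sets 1:1 allocation. Section 2.8 (Statistical analysis) compares normally distributed continuous variables by Student's t-test, with significance at a two-sided P below .05. It mentions no margin.

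**The concern.** A paragraph that gives an expected difference, a smaller boundary value, a one-tailed test at 0.025 and a specially named test has the layout of a superiority-by-margin calculation. A reader who takes it that way subtracts 4 from 6.5 and finds that 216 patients fall far short. A reader who takes 6.5 as the difference to detect against zero finds 216 far more than needed. Neither arrives at the stated size.

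The gap matters because the 90% power claim belongs to one hypothesis only, and the paragraph does not say which. If the null value is not fixed in advance, the result could be judged afterwards against zero or against 4 points, and the trial's power differs greatly between the two. The stray 226 also leaves the recruitment target unclear.

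**Working it through.** **Inputs** (section 2.7 unless noted): SD 9; candidate differences 6.5 and 4; one-sided alpha 0.025; power 0.90; 1:1 allocation (section 2.1); two-sample t-test (section 2.8); 10% loss.

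**Formula.** The normal approximation per arm is n = 2 × (1.960 + 1.282)² × SD² / d², where d is the distance between the assumed true difference and the null value. With SD 9 this is n = 1702.2 / d². The exact t-test calculation (noncentral t) adds about one patient per arm.

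**Reproducing the plan's figure.** Take d = 4 against zero: 1702.2 / 16 = 106.4 per arm, so 107. The exact calculation gives 108 per arm, **216 in total**, with power 90.2%. Then 216 / 0.90 = **240**. Both of these stated numbers are recovered exactly.

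**The other combinations of the stated inputs.**

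| Assumed difference | Null value | d | n per arm (normal, before rounding) | n per arm (exact t) | Total | Power at 216 |
|---|---|---|---|---|---|---|
| 4 | 0 | 4 | 106.4 | 108 | 216 | 90.2% |
| 6.5 | 0 | 6.5 | 40.3 | 42 | 84 | above 99.9% |
| 6.5 | 4 | 2.5 | 272.4 | 274 | 548 | 52.9% |

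**Power by hand at 108 per arm.** The standard error is 9 × √(2/108) = 1.225.

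- For d = 4, 4 / 1.225 = 3.27. This exceeds 1.960 by 1.31, so power is about 90%.
- For d = 2.5, 2.5 / 1.225 = 2.04. This exceeds 1.960 by only 0.08, so power is about 53%.

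On the margin reading, power would be 54.7% with 226 evaluable patients and 57.3% with 240.

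**The number 226.** If it were the evaluable number, 226 / 0.90 = 251 would be randomised, not 240. If it were the randomised number, 226 × 0.90 = 203 would be evaluable, not 216. None of the three combinations above gives it.

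**Sensitivity to the SD.** The text says only "a 9% standard deviation with respect to LVEF", not whether this is the SD of LVEF or of its change from baseline, while the primary endpoint in section 2.6.1 is a change. On the margin reading, 216 would reach 90% power if the SD were about 5.6. If 9 were the SD of LVEF at a single time, and were the same at both times, the SD of the change would be 9 × √(2(1 − r)), where r is the correlation between baseline and follow-up. The article gives no r, so the values below are assumptions:

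| r | SD of change | Power at 216, d = 2.5 |
|---|---|---|
| 0.5 | 9.0 | 53% |
| 0.7 | 7.0 | 75% |
| 0.8 | 5.7 | 89% |

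**The case against.** The strongest reply is that the sample size is right and only the prose is loose. A 4-point difference against zero reproduces 216 exactly, and the 10% loss takes it exactly to 240. Section 2.8 plans an ordinary two-sided t-test without a margin. On this view 6.5 is background evidence, 4 is a more cautious target, and the 90% power is true. One-sided 0.025 and two-sided 0.05 are also equivalent for this purpose. This stands as the better-supported reading, and for that reason the paragraph should not be called underpowered outright.

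Four stronger statements are tempting, and the document does not support them.

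- A reader might infer that the trial has 53% power and not 90%. That holds only if 4 is a margin subtracted from 6.5 and 9 is the SD that applies to the comparison. Section 2.7 never says the first and leaves the second open.
- A reader might say that three sizes conflict. In fact 216 and 240 are the evaluable and randomised forms of one calculation; only 226 is out of line.
- A reader might take the meta-analysis figure in the Discussion ("resulted in an overall improvement of 4.44% absolute LVEF points") as the likely true effect and conclude that the trial has almost no chance of exceeding a 4-point boundary. The Discussion reports that figure as an improvement after successful recanalisation. It is not shown to be a difference between the two randomised strategies, so no power figure should rest on it.
- A reader might say that no use of both 6.5 and 4 could ever give 216. As the sensitivity table shows, an assumed correlation near 0.8 would come close, though the article states nothing of the kind.

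The reply does not account for a 6.5-point difference presented as an input but not used, for a target difference labelled as a boundary, or for 226.

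**Conclusion.** The point holds as an internal contradiction in section 2.7. The listed inputs do not jointly yield the listed size: 216 requires 4 points against zero, with 6.5 unused. The consequence depends on what the 4 means. If it is the target difference, the stated 90% power is correct (90.2%) and the fault lies in the description. If it is a superiority margin with 6.5 expected, 548 evaluable patients would be needed and 216 gives about 53%, some 37 percentage points below the claim. Whichever is meant, 226 is wrong or unexplained.

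These figures assume equal arms, one-sided alpha 0.025 and an SD of 9 for the quantity actually compared. The sample size and its power basis are figures the trial relies on, so the paragraph needs correcting even though the better-supported reading leaves 216 and 240 intact.

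**What to change.** Rewrite the paragraph in section 2.7 so that it names the null value tested.

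- **If the null value is zero**, as section 2.8 implies: state that 216 evaluable patients (108 per arm; 240 randomised to allow for 10% loss) give 90% power for a 4-point between-group difference with SD 9, at one-sided 0.025 (two-sided 0.05). Say whether 9 is the SD of LVEF or of its change. Label 6.5 as background evidence not used in the calculation, and drop the word boundary.
- **If a 4-point margin is really to be tested**: say so in section 2.8, and restate the power at 216 as about 53% with SD 9. If 9 is not the SD of the quantity compared, give the one that is and recompute the power from it.
- **In either case**: remove 226, or correct it to 216 evaluable and 240 randomised, and replace the undefined name of the test with the actual hypothesis.

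The cost is the wording of one paragraph, plus a sentence in section 2.8 if the margin is kept. In that case the stated power becomes less favourable. No additional patients are proposed.

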#### PCI procedure

2.4.1

Experienced operators have been designated to ensure that the success rate of CTO-PCI is above 80%. Procedural success is defined as resulting in residual stenosis of <10% with thrombolysis in myocardial infarction grade 3 flow, in the absence of dissection and thrombosis. The use of a DES and specialized devices will be left to the discretion of the operator.

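### The 10% loss allowance leaves out the failed CTO-PCI and MACE exclusions and the control crossovers that the protocol provides for, so 90% power for a 4-point LVEF difference has almost no margin and is probably not reached

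*Protocol article*

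**What the plan says.** Section 2.7 sizes the trial on LVEF: "LVEF has been taken into consideration for the calculation of sample size". Its inputs are these: "Previous studies revealed a 6.5% mean difference between the two experimental groups and a 9% standard deviation with respect to LVEF", and "The optimal boundary value for LVEF was set to 4" per cent. It asks for 216 cases at one-sided α 0.025 and power 0.90, then adds one allowance: "240 patients will be randomized, and a 10% loss is expected to occur throughout the 1-year follow-up period". It gives the aim as follows: "The main purpose of this trial is to investigate the effect successfully opening concurrent CTO lesions on cardiac function in patients with MVD".

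Three other places bear on how many patients reach the primary analysis and what contrast they provide.

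- Section 2.4.1, on procedural success: "Experienced operators have been designated to ensure that the success rate of CTO-PCI is above 80" per cent. Section 2.9 repeats this target.
- Section 2.8, on analysis sets: the full analysis set keeps everyone in the randomised group. Per-protocol patients whose CTO-PCI fails count for baseline description but not for the primary analysis. It then adds, without naming a set: "Patients will not be included in the primary analysis if the MACEs occur". Section 2.6.2 defines MACE broadly, including heart failure and cardiac rehospitalisation.
- Section 2.2, on monitoring: "those with persisting clinical symptoms occurring within one month of OMT will undergo PCI of CTO artery".

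**The concern.** The 10% is described as loss over the follow-up year, and it is fully used in going from 240 to 216. The protocol then gives further routes by which patients leave the primary analysis (failed procedure, MACE) or by which the treatment contrast shrinks (failures and control crossovers, if patients are kept as randomised). No rate for any of these enters the calculation.

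At stake is how a non-significant result would be read. If the report says the trial had 90% power while the protocol's own rules deliver less for the difference it was sized on, a null finding will be given more weight than it deserves.

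**Working it through.** **Inputs from the protocol.** SD 9 points; boundary value 4 points; cited difference 6.5 points; one-sided α 0.025; power 0.90; 216 evaluable; 240 randomised; 10% loss (all 2.7); 1:1 allocation (2.1); success above 80%, so failures below 20% (2.4.1).

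**Assumed, because the protocol gives no figure.** MACE exclusions 10%; control crossover 10%. A 10% failure rate is used as a milder case inside the protocol's bound.

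**Method.** Two-sample t-test, noncentral t, with noncentrality δ / (SD × √(1/n₁ + 1/n₂)).

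**1. Reproducing the plan's figure.** With δ = 4, SD 9 and 108 per arm, noncentrality = 4 / (9 × √(2/108)) = 3.27 and power is 90.2%. With 107 per arm (214 in total) it is 89.9%. So 216 is the smallest equal-arm total that reaches 90% for 4 points. The allowance is 216 / 0.9 = 240. Other readings do not give 216: 6.5 points against zero needs 84 in total, and a true 6.5 against a 4-point margin (net 2.5) needs 548.

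**2. Size of the allowance.** 10% of 240 is 24 patients. At the success floor, failures alone are 20% of 120 = 24, which is the whole allowance before anyone is lost.

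**3. Failures and MACE excluded, 4-point effect, after 10% loss.** The CTO-PCI arm is 108 × (1 − f) × (1 − m) and the control arm is 108 × (1 − m), where f is the failure rate and m the MACE rate.

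| Failures f | MACE m | n per arm | Power |
|---|---|---|---|
| 10% | 0 | 97 / 108 | 88.6% |
| 20% | 0 | 86 / 108 | 86.5% |
| 10% | 10% (assumed) | 87 / 97 | 85.1% |
| 20% | 10% (assumed) | 78 / 97 | 82.8% |

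**4. Patients kept as randomised, 108 per arm.** This step supposes that the 4 points is an effect of successful opening, that failures gain nothing, and that crossovers (rate c) succeed at the same rate as the CTO-PCI arm. The as-randomised difference is then 4 × (1 − f) × (1 − c).

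| Failures f | Crossover c | Difference | Power |
|---|---|---|---|
| 10% | 0 | 3.6 | 83.3% |
| 20% | 0 | 3.2 | 73.9% |
| 20% | 10% (assumed) | 2.88 | 64.8% |

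**5. The same checks with 6.5 points tested against zero.**

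- As randomised, 20% failures: 6.5 × 0.8 = 5.2 points, power 98.8%.
- As randomised, 20% failures and 10% crossover: 6.5 × 0.8 × 0.9 = 4.68 points, power 96.7%.
- Exclusion rule, 20% failures and 10% MACE (78 / 97): power above 99%.

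**The case against.** The strongest counter-argument is that section 2.7 never calls 4 points the detectable difference. It calls it a boundary value and cites 6.5 points as the difference between groups. On 6.5 points against zero, power is ample even after heavy attrition. This stands, and it limits the point to a 4-point effect. It does not remove the point, because 4 is the only one of the stated figures that gives 216. Reading 4 as a superiority margin does not help either: power would be about 53% with 216 before any attrition.

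Other objections have partial force.

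- *The 20% is a ceiling.* True. The introduction reports success above 90% at experienced centres, and at 10% failures the exclusion rule costs less than two points of power.
- *Loss is not defined.* Deaths are both MACE and loss, so a separate 10% for each overlaps somewhat. If the whole allowance went on 20% failures and nobody was lost, power would be 89.8%. But the text ties the 10% to the follow-up year and does not say that it covers procedural failures.
- *The dilution may be counted twice.* If the planning difference already compares groups as randomised, failures are in it and step 4 does not apply. The protocol does not say which it is.
- *The primary set is unclear.* The failure exclusion is worded for the per-protocol set, so one cannot insist that 216 patients could never be in the primary analysis.

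A reader might infer that the stated power is missed whatever the true effect, or that the trial's real power is about 65%. The documents support neither. The first fails at 6.5 points. The second needs a crossover rate that the protocol does not give and an assumption about what the 4 points means.

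**Conclusion.** The point holds in conditional form. The arithmetic in 2.7 is right (108 per arm, 90.2%, 216 / 0.9 = 240); what is incomplete is the set of assumptions behind it. For a 4-point difference, any exclusion or dilution of practical size beyond the 10% loss takes power below 90%.

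The shortfall is modest under the exclusion rule: 88.6–86.5% for 10–20% failures, and lower with MACE exclusions. It is larger as randomised, at 83–74%, but only if the 4 points is an effect of successful opening with none in failures. Every figure that uses a MACE or crossover rate is illustrative. The direction is certain; the size depends on rates and definitions that the protocol should state.

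**What to change.** In section 2.7:

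1. Say whether the 90% refers to 4 or to 6.5 points, and whether that difference is as randomised or for successful opening.
2. State the assumed CTO-PCI failure, MACE and crossover rates, and what the 10% loss covers.
3. Restate power for 240 randomised as a range under those labelled assumptions, for the analysis set that 2.8 names as primary. Until that set is settled, show both sets and both effect sizes.

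The 65% figure should not be printed as the trial's power; it is one scenario. Sections 2.2, 2.4.1, 2.7 and 2.8 need to be reconciled with one another, leaving the clinical crossover rule as it is. Restating power does not cure any bias from excluding patients after randomisation, which is a separate matter for 2.8.

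The cost is protocol wording and a less favourable stated power. This correction needs no increase in the number randomised.
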